## Abstract

**Background:**

Advanced cancer significantly impacts patients’ and family caregivers’ quality of life. When patients and caregivers are supported concurrently as a dyad, the well-being of each person is optimized. Family, Outlook, Communication, Uncertainty, Symptom management (FOCUS) is a dyadic, psychoeducational intervention developed in the United States, shown to improve the well-being and quality of life of patients with advanced cancer and their primary caregivers. Originally, a nurse-delivered in-person intervention, FOCUS has been adapted into a self-administered web-based intervention for European delivery.

**Objective:**

The aims of this study are to (1) adapt FOCUS to the Australian context (FOCUSau); (2) evaluate the effectiveness of FOCUSau in improving the emotional well-being and self-efficacy of patients with advanced cancer and their primary caregiver relative to usual care control group; (3) compare health care use between the intervention and control groups; and (4) assess the acceptability, feasibility, and scalability of FOCUSau in order to inform future maintainable implementation of the intervention within the Australian health care system.

**Methods:**

FOCUS will be adapted prior to trial commencement, using an iterative stakeholder feedback process to create FOCUSau. To examine the efficacy and cost-effectiveness of FOCUSau and assess its acceptability, feasibility, and scalability, we will undertake a hybrid type 1 implementation study consisting of a phase 3 (clinical effectiveness) trial along with an observational implementation study. Participants will include patients with cancer who are older than 18 years, able to access the internet, and able to identify a primary support person or caregiver who can also be approached for participation. The sample size consists of 173 dyads in each arm (ie, 346 dyads in total). Patient-caregiver dyad data will be collected at 3 time points—baseline (T_0_) completed prerandomization; first follow-up (T_1_; N=346) at 12 weeks post baseline; and second follow-up (T_2_) at 24 weeks post baseline.

**Results:**

The study was funded in March 2022. Recruitment commenced in July 2024.

**Conclusions:**

If shown to be effective, this intervention will improve the well-being of patients with advanced cancer and their family caregivers, regardless of their location or current level of health care support.

**Trial Registration:**

ClinicalTrials.gov NCT06082128; https://clinicaltrials.gov/study/NCT06082128

**International Registered Report Identifier (IRRID):**

PRR1-10.2196/55252

## Introduction

### Overview

Advanced cancer is a “family affair” significantly affecting the well-being of the person with cancer and their family [1]. Family caregivers are at the core of patient care; they are typically unpaid laypeople, comprising close family members or friends or others who provide a significant level of support (practical, social, or emotional) to the person with cancer. Additionally, their contributions alleviate some of the burden on the Australian health care system, resulting in significant cost savings [2]. As a result, addressing the needs of both patients and their family caregivers is a priority in many countries, with established standards, policies, and guidelines [3-5].

Furthermore, the World Health Organization advocates that palliative care should be “family centered,” enhancing the quality of life (QoL) of the patient and their family caregivers [6], and includes supporting those still receiving curative treatment in addition to those receiving end-of-life (EoL) care [7]. Palliative care, when effectively delivered, can restore choice regarding options for care [8], improve patients’ and caregivers’ sense of control, self-efficacy, coping ability, communication about the illness, and reduce emotional distress [9]. Research has shown the benefits of early access to palliative care for patients, their family caregivers, and the health care system; there has been an increased and proactive approach to early integration of palliative care to improve QoL and symptom management of patients and family caregivers [7]. Hence, intervening earlier in the disease trajectory to assist the family unit in preparing for and responding to the implications of life-threatening illness constitutes best practice.

Despite the policy, clinical and research evidence advocating a family approach to palliative care, systemic inadequacies such as the inability of many family caregivers to access health professional support and fragmented, inconsistent, variable palliative care services, along with the lack of preparation for death have impeded family-centered care [10]. Patients may undergo potentially unnecessary treatment, report high levels of pain, difficulty coping, poor physical and emotional health, and their EoL wishes not always upheld [10]. This translates to many caregivers reporting high emotional distress, unmet needs, and difficulties with providing complex home-based care, especially during the advanced stages of illness and EoL [11]. Around 40% of caregivers are reported to experience psychological distress [12] which is typically underrecognized [13]. Furthermore; these impacts may be more pronounced in underserved groups.

The overwhelming majority of Australians would prefer to die at home [14], yet Australian acute hospitals provide EoL care to approximately 50% of people who die [15]. Comprehensive family support is a key factor in determining whether the preference for home care and death can be realized [16]. Yet, effective systematically applied psychosocial support for family caregivers in the EoL context is still underdeveloped [16,17].

Patients and family caregivers experience illness together, with 1 person’s ability to cope affecting the other’s [18]. In a longitudinal study of dyads including people with advanced cancer and their caregivers, caregiver mental health at baseline significantly influenced patient mental health 3 months later [11], while in a study of dyads affected by brain cancer, greater caregiver competence in the caregiver role predicted longer patient survival [19]. Dyadic interventions, targeting the patient and family caregiver together, are more likely to result in better outcomes for both parties than single-target interventions and may be more cost-effective [18,20,21]. Consequently, dyadic interventions focusing on the QoL of both the patient and caregiver from the point of advanced disease diagnosis are necessary to promote well-being and cost-effective care.

Historically, much of the psychological and psychoeducational palliative care intervention research has been delivered in person, with demonstrated improvements in patient QoL [22] and family caregiver well-being, sense of preparedness, reduction of unmet needs, and more favorable bereavement outcomes [21,23-25]. While these in-person delivered interventions produce promising results, they can be time and resource-intensive. These resource requirements constitute a major barrier to longer-term implementation and integration of these interventions into the health care system, particularly in the context of current shortages of staff and other resources.

Digital health interventions offer an innovative modality for the delivery of health care services [26]. They provide considerable resource advantages to in-person interventions [27] such as improving, information-sharing, decision-making, and communication [26,28,29]. Advantages for users also include lower cost of delivery, greater reach (including for rural and remote areas), convenience, less travel time, reduced risk of infections due to reduced exposure associated with face-to-face consultations, and recipients feeling more empowered [27,29]. A meta-analysis of internet therapy studies has provided strong support for the adoption of internet-based psychological interventions [30] and the increasing use of digital health has ushered in a new era of patient-centered cancer care that moves beyond the traditional in-person care model [31].

Digital health within the context of palliative care should not be considered a replacement for, but complementary to, in-person care in this con (which has numerous benefits) [29]. Indications are that digital health communication in this context may result in patients and caregivers receiving more reliable information; it can be more feasibly applied; and at organizational and societal levels, digital health may contribute to more efficient and equitable use of resources [29]. Furthermore, disseminating dyadic interventions via the internet and other technologies may be more scalable from a health systems perspective [18]. Reduced labor costs, as well as lower ongoing program charges, suggest that the longer-term cost-effectiveness of digital health interventions compares favorably with traditional in-person care [18]. However, compared to the rapid increase of digital health interventions in other areas of health care, there is limited application of digital health interventions within advanced cancer and palliative care settings. No rigorously tested interventions applied systematically in Australia have targeted the psychosocial well-being of the patient-caregiver dyad [26,29]. There is an urgent need, therefore, to develop evidence-based, dyadic digital health approaches that are meaningful, accessible, and maintainable for integration into the Australian health system.

### Focus Intervention Background

The Family, Outlook, Communication, Uncertainty, Symptom management (FOCUS) intervention has been developed in accordance with guidelines for complex interventions [32-36]. Co-designed with consumers, patients, and family caregivers, the intervention consists of five core components underpinning the FOCUS acronym and they are (1) supporting *Family* involvement, (2) supporting *Outlook* and meaning, (3) increasing *Coping* effectiveness, (4) reducing *Uncertainty*, and (5) *Symptom* management. The original in-person FOCUS program was developed in the United States as a nurse-delivered in-person intervention, being multicomponent and psychoeducational in its framework, and providing tailored informational and emotional support to patients with advanced cancer and their family caregivers [32]. The efficacy of this in-person FOCUS intervention was demonstrated in 3 randomized control trials and 2 pilot effectiveness studies conducted in the United States [32-35,37], with the patient-caregiver dyads reporting significantly improved QoL and well-being, less negative appraisal of illness and caregiving, reduced uncertainty and hopelessness, improved communication, and enhanced self-efficacy. To make the FOCUS (United States) intervention more accessible, the main component (family involvement) of this in-person intervention was then adapted into a tailored, digital or web-based format [38]. Significant intervention effects were found in a pre-post study on dyads’ QoL, emotional distress, perceived benefits of illness or caregiving, and caregivers’ self-efficacy [38].

The strong empirical base and use of the FOCUS (United States) intervention have been acknowledged by the European Union (EU) through successful grant funding awarded to test European-adapted versions of both programs (in-person [FOCUS+] and digital [iFOCUS] in a phase 3 trial, currently being conducted across 6 countries (England, Ireland, Belgium, Denmark, the Netherlands, and Italy) [39-41].

For this study, we aim to test the FOCUS EU digital version (iFOCUS) for the Australian setting (“FOCUSau”), given the need to reach regional and rural areas and address the cost-effectiveness and maintainability issues that arise for in-person interventions.

### Research Aim and Hypotheses

We seek to determine the effectiveness and maintainability of a digital health intervention (iFOCUS) aimed at improving the well-being of patients with advanced cancer and their primary family caregivers. Our objectives are to (1) adapt iFOCUS to the Australian context to create FOCUSau; (2) examine the effectiveness of FOCUSau in improving the well-being (primary outcomes are emotional well-being and self-efficacy) of patients with advanced cancer and their primary family caregiver, compared to the control group (usual care); (3) compare the types and costs of health services used by participants in the intervention and control group; and (4) assess the acceptability, feasibility, and scalability of FOCUSau in order to inform the maintainable implementation of the intervention within the Australian health care system.

Our hypotheses are that compared to the control group, patent-caregiver dyads in the intervention group (who receive the intervention in addition to usual care) will, at 12 weeks follow-up, report (1) higher levels of emotional well-being and self-efficacy (ie, confidence in managing illness; primary outcomes) and (2) higher QoL, less negative appraisal of illness or caregiving, better communication about the illness, and improved coping ability (secondary outcomes). In addition, FOCUSau will be cost-effective compared with the control group in terms of the incremental cost (change in health care use) per additional participant with a meaningful change in (1) emotional well-being and (2) self-efficacy.

## Methods

The study addresses the objectives in 3 stages.

### Stage 1: Adaptation of iFOCUS to the Australian Health Care Setting (Objective 1)

The adaptation of iFOCUS to create FOCUSau will involve appraisal of the intervention by consumer representatives and research team participants along with detailed feedback to inform modifications. The process will be underpinned by the ADAPT process [42] whereby we will also evaluate the quality, acceptability, appropriateness, comprehensibility, accessibility, and feasibility of the intervention before and after adaptation. We have concurrently reviewed the compatibility of the intervention software with Australian digital health infrastructure and ensured alignment with Australian standards for digital accessibility, security, privacy, and shareability of personal data, and capacity to interoperate with other systems.

Consumer representatives and research team participants (n=16) viewed the iFOCUS intervention and provided detailed feedback to inform the modifications. Participants also completed the Adapted Mobile Application Rating Scale [43] and the Theoretical Framework of Acceptability questionnaire [44] and commented on the quality, acceptability, appropriateness, comprehensibility, accessibility, and feasibility of the intervention before and after adaptation. We collected data using REDCap (Research Electronic Data Capture; Vanderbilt University) [45] and analyzed data using descriptive statistics, thematic analysis [46], and content analysis [47]. Data analysis led to suggestions for modifications to the intervention which were voted favorably by participants. The full method and results of the adaptation study will be reported elsewhere.

### Stage 2: Pragmatic Phase 3 Hybrid Effectiveness-Implementation Trial of FOCUSau (Objectives 2 and 3)

#### Design

We chose to conduct a Hybrid type 1 implementation study that included a Phase 3 effectiveness component and an observational implementation study [48]. This integrated research design includes digital health evaluation [49] to account for the interaction between conventional health effects and human-computer engagement [50]. This includes (1) randomization of participating dyads to the intervention versus standard care (control group), to examine FOCUSau effectiveness in relation to clinical outcomes and health service use, while simultaneously (2) exploring acceptability, feasibility, maintainability, and scalability of the intervention—that are recognized in both implementation science methods [48] and digital health evaluation methods [51]. Hybrid designs have a dual focus—a priori assessment of clinical effectiveness and implementation [48]. These pragmatic designs offer novel ways of testing intervention effectiveness and potential uptake and are recommended for multisite psychosocial-related interventions in cancer care [52].

#### Participants

Patient inclusion criteria are diagnosis of advanced cancer; older than 18 years of age; able to comprehend written or spoken English; no visual, hearing, or cognitive impairment that would preclude participation; can commit to research participation requirements (including data collection and completion of the FOCUSau intervention if randomized to that group); able to access the internet (on their own desktop computer, laptop computer, or tablet device); and able to identify a primary support person or caregiver, who is an unpaid individual (not necessarily a partner or family member) who is providing them with physical, social, or emotional support. The patient exclusion criterion is involvement in an advanced cancer nondrug trial that focuses on improving QoL. Family caregiver inclusion criteria are identified by the patient as their primary support person who is related to them biologically, legally, or emotionally, and is willing to accept this support role; aged older than 18 years; no visual, hearing, or cognitive impairment that would preclude participation; commits to research participation requirements; and is able to access the internet. Dyad inclusion criterion is the capacity to effectively use the internet (as determined through a short practical internet-based exercise as part of the screening and consent process).

#### The FOCUSau Intervention

##### Aim and Core Features

The overall aim is to enhance dyads’ emotional well-being and self-efficacy, addressed by 5 core components of the intervention [32]. The transactional model of stress and coping underpins the intervention [53].

##### Delivery Mode, Dose, and Timeline

The intervention is self-administered, completed autonomously via the internet by the patient and caregiver dyads. It encompasses 4 prescribed consecutive sessions (with 3 weeks between each session) over a period of 12 weeks that collectively cover the 5 core components; the core content of which is outlined in Figure 1. The sessions are completed simultaneously by the patient and family caregiver, together at a computer. At the beginning of each session, a computer prompt (wizard) explains how dyads can navigate through the sessions. Access to the 4 sessions is provided via an automated link sent by an email. The content of the sessions is written at a lower secondary education reading level, using principles of plain language. Audio instead of text provision of material is also available to allow for participation by those with visual impairment. Written content is complemented by images and videos of patients and caregivers reflecting on their advanced cancer experience which is linked to 5 core components.

**Figure 1 figure1:**
[figure not shown]
Intervention overview.

##### Additional Resources

Dyads are provided with an internet-based personal workbook containing information tailored to their responses to questions completed during the internet sessions. Any information sheets that the dyad indicated as “of interest to them” during the internet sessions are included as a hyperlink in their personal workbook which also contains evidence-based local advanced cancer-related resources. Assistance via a helpdesk (via email or telephone) is available to resolve any technical difficulties with accessing the internet-based materials.

##### Tailoring of the Intervention

Tailoring enhances the intervention’s efficacy by providing dyads with information personally relevant to them. Three types of tailoring strategies are used—personalization, tailored feedback, and content matching [54]. Participants receive tailored individual and dyadic messages according to their own demographic characteristics (age, sex, and dyadic relationship) provided at study enrollment and their responses to questions within the sessions.

#### The Control—Usual Care

Participants in the control group will receive usual care. Usual care in advanced cancer care is known to be heterogeneous. Nonetheless, we will collect relevant health services usage data (see below) to describe and compare the control and intervention arms.

#### Setting and Recruitment Procedures

The patient-caregiver dyads will be recruited via two methods that are (1) referral from hospitals or (2) self-referral. For method 1, approximately 6 hospitals and cancer centers (metropolitan and regional) across several states of Australia will be selected. The specific selection of institutions will be undertaken by the Cancer Symptoms Trials (CST) group (a national cooperative trials group) as the trial coordinating center. The CST will undertake a feasibility assessment process to ensure institutions are selected on their ability to demonstrate that they have the internal resources and patient population to refer sufficient dyads to achieve the site-specific sample size and broad coverage of services across Australia. As part of the CST site selection process, participating institutions will identify multidisciplinary staff in relevant departments to undertake an initial eligibility screen. The study will be verbally explained to eligible patients who receive a brief written project summary. With their permission, the contact details of patients interested in the study will be submitted to the project website by the relevant referring clinician. Thereafter the patient will be contacted by a research officer who will undertake the screening and consenting process incorporating obtaining permission to contact the patient’s primary family caregiver to seek their interest in participating, then scheduling a video meeting with the dyad which will also serve as a further check of their capacity to engage in an internet intervention. If all inclusion criteria are met, electronic consent via standard ethical requirements will be undertaken.

For the self-referral recruitment method, patients who have been made aware of the project (but have not been officially screened by a clinician) may self-refer via a form on the project website. These patients will be made aware via consumer, caregiver, cancer advocacy groups, or social media advertisements. A research officer will then review the self-referral form and liaise directly with the patient to advise if they meet the criteria and if so, recruiting and consent procedures will be undertaken as per method 1. There will be a second videoconference arranged (after consent and subsequent randomization) to explain to the dyad which group they have been allocated to and brief orientation to the FOCUSau platform and the associated data collection methods.

#### Allocation and Blinding

Following informed consent and completion of baseline measures, block randomization will occur via an embedded randomizer within the FOCUSau platform to create the randomization table based on blocks of multiplicators of 2 and blocks of 4, 6, and 8. The block randomization method is designed to randomize subjects into groups to ensure a balance in sample size across groups over time. A research officer will initiate the randomization process which will involve logging into the FOCUSau platform, entering relevant participant details and then block randomization will occur. Due to the nature of the intervention, the patient-caregiver dyads cannot be blinded to allocation. Data collection will occur electronically and the research team will remain blind to which trial arm the dyads were randomized until the end of the final data-collection point. The first 10 consented dyads who are allocated to the intervention group will additionally be invited to participate in the final step of the aforementioned intervention adaptation process and be provided with a specific (additional) participant information sheet and consent form.

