### Stage 3: Acceptability, Feasibility, and Scalability of FOCUSau (Objective 4)

Our approach is underpinned by a conceptual framework that highlights the link between acceptability, fidelity and feasibility, and potential implementability [66]. An investigation of fidelity will also inform internal validity and thus our interpretation of the effectiveness findings. If prospective acceptability, uptake and engagement with the intervention are moderate (based on conventional cutoff scores of 50%) [67,68], then FOCUSau is feasible to deliver in other settings; if participants receive and comprehend FOCUSau as designed (ie, fidelity is high), then the effectiveness findings will represent a valid test of the intervention; if participant retention and retrospective acceptability are high, then FOCUSau is likely to be maintainable; and if FOCUSau is cost-effective and additional workforce requirements are minimal, then the intervention is likely to be scalable. Acceptability is “the extent to which people receiving FOCUSau consider it to be appropriate, based on anticipated (prospective) or experienced (retrospective) cognitive and emotional responses to the intervention” [69]. Informed by a new and influential theoretical framework of acceptability [69], we will pilot test a questionnaire [44] to be administered at baseline and follow-up (T_0_ and T_2_). As acceptability is ideally assessed both quantitatively and qualitatively [36], a diverse subsample of participants (~30 dyads) will be recruited from the intervention group and be interviewed via videoconference immediately following the completion of FOCUSau (T_1_), to gain a greater insight into intervention acceptability, including potential for further enhancements. As for the uptake, we will document the recruitment process, including reasons for accepting or declining participation and examine the sociodemographic profile of dyads invited to participate in the trial, capturing our capacity to reach relevant populations (with lower socioeconomic status, cultural minorities, and from rural or remote locations). We will also use the aforementioned T_1_ interviews to explore barriers and enablers to uptake by dyads. Interview topic guides (1 for patients; a parallel guide for caregivers) will be informed by the TDF of behavior change [65]. Intervention fidelity encompasses whether the intervention is delivered and received as planned [70]. We will document communication between trial managers and participants, whether for technical problem-solving or for other reasons, to assess whether components have been added to FOCUSau as designed. Aspects of adherence (intervention as received) are built into the FOCUSau internet module and include a readily accessible “help” function. Dyads who experience problems with onboarding for the FOCUSau sessions will receive help from the trial manager via phone; they will confirm their presence and indicate whether they are using the computer or phone; dyads who exit an FOCUSau session before completion will be sent a reminder email or text message. Completion rates of individual FOCUSau sessions will be monitored.

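### The article claims that the whole research team stays blind until 24 weeks, but its own procedures need or reveal the allocation before then

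*Protocol article*

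**What the plan says.** In Allocation and Blinding, the article acknowledges that dyads cannot be masked. It then says that data are collected electronically and that "the research team will remain blind to which trial arm the dyads were randomized until the end of the final data-collection point". Data Collection: Primary and Secondary Psychosocial Outcomes puts the last collection point at T2, 24 weeks after baseline. T1, the primary time point, is at 12 weeks.

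Elsewhere the article describes these procedures:

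- **Setting and Recruitment Procedures:** a second videoconference, after randomisation, is held "to explain to the dyad which group they have been allocated to and brief orientation to the FOCUSau platform".
- **Allocation and Blinding**, directly after the blinding sentence: "The first 10 consented dyads who are allocated to the intervention group will additionally be invited" to join the last step of the adaptation work, with their own information and consent form.
- **Stage 3:** "Dyads who experience problems with onboarding for the FOCUSau sessions will receive help from the trial manager via phone".
- **Stage 3:** "a diverse subsample of participants (~30 dyads) will be recruited from the intervention group" and interviewed at T1, once they have finished the programme.
- **Ethical Considerations:** when a patient dies, caregivers in the intervention arm are told that they need not carry on with the study.

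A research officer handles screening and consent ("the patient will be contacted by a research officer who will undertake the screening and consenting process") and starts the randomisation ("A research officer will initiate the randomization process which will involve logging into the FOCUSau platform").

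**The concern.** The blinding sentence covers the research team as a whole and runs to week 24. Each procedure listed above requires someone working on the study to know at least some allocations. Nobody can tell a dyad its group, or select dyads for interview because they are in the intervention arm, without knowing the arm.

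Three things are at stake. First, a reader of the trial report, or someone judging risk of bias, would credit the trial with a safeguard that it does not have in the form stated. Second, participants know their arm and rate their own outcomes, so the remaining protections are even-handed contact and follow-up and unbiased handling of withdrawals, missing data and analysis choices. These matter here: the sample size section allows for 20% loss by T1, and the Limitations section foresees withdrawals by dyads who were not given the intervention. Third, the interviews take place at T1, in one arm only. An intervention dyad interviewed about the programme before filling in its T1 questionnaires could answer them differently, and control dyads have no such contact.

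**Working it through.** No formula applies. The check sets each activity against the period for which blinding is claimed (randomisation to week 24) and asks two questions: does the activity need or reveal the arm, and does it come before T2?

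| Activity | Needs or reveals the arm? | When | Dyads affected |
|---|---|---|---|
| Second videoconference | Yes, disclosing the group is its purpose | After randomisation, before the programme starts | All, on the natural reading (see below) |
| Invitation to the first 10 intervention dyads | Yes, selection is by allocation | Date not given; tied to early enrolment | 10 |
| Trial manager help with sessions | Yes, only intervention dyads have sessions | During the 12-week programme | Those with onboarding problems; number not given |
| Acceptability interviews | Yes, sampled from the intervention arm | T1, which is 24 − 12 = 12 weeks before T2 | About 30 |
| Advice after a death | Yes, it differs by arm | Before T2, since it concerns not continuing in the study | Number not given |

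**Size of the numbered items.** The plan recruits about 433 dyads. With equal arms, as the target of 173 per arm implies, that is 433 / 2 ≈ 216 in the intervention arm. The interviews reveal about 30 / 216 ≈ 14% of that arm and the adaptation invitation 10 / 216 ≈ 5%. On their own, these two would be local exceptions to blinding.

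**The videoconference decides the matter.** The sentence stands at the end of the self-referral paragraph, so one could confine it to self-referred dyads. Its wording is general, however, and that section gives no other way for a dyad to learn its group. On that reading, the arm of every randomised dyad is known to whoever holds the call, before T1 and well before T2.

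**Not counted.** Starting the randomisation is left out of the table. The article says that the officer enters the details and randomisation then follows; it does not say that the result is shown to the officer. Reminders for unfinished sessions are also left out. No sender is named, and the session links themselves are sent automatically.

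**Result.** All five activities need or reveal allocation. Four fall before T2 by their stated or implied timing. The fifth, the adaptation invitation, is undated but tied to early enrolment. The claim that the whole team is blind until T2 is incompatible with them.

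**The case against.** The strongest reply is that the research team is never defined. It could mean the investigators and analysts, with the research officer, trial manager and interviewers treated as operational staff outside the blind. The article does not say who holds the second videoconference or the interviews. A reader might infer that one and the same group randomises, discloses, supports and interviews, and so that nobody is blind and the masked share of the sample is nil. The documents do not support that. The single group is an inference, and one person on a call is not the whole team. A blind analyst is neither stated nor excluded. This part of the reply stands, and it limits the point to blinding of the whole team. It does not rescue the sentence, which makes no exception and describes no separate unblinded group. If the narrower meaning is intended, the text has to say so.

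A reader might also infer that staff who know the arm chase the T1 and T2 questionnaires. The article describes no such chasing. The only reminders that it mentions concern unfinished intervention sessions. Differential follow-up is therefore a risk to guard against, not something that the plan lays down.

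The second reply is that staff blinding hardly touches the result, because both primary outcomes are electronic self-reports by dyads openly described as unblinded. That is largely right. Correcting the sentence changes no measurement, and participant unblinding is the larger source of bias in any case.

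The third reply is that analyst masking and operational order belong in the analysis plan or full protocol, which are not shown. Their absence is indeed no fault. The point here is an explicit statement that other parts of the same article contradict, and a further document cannot make the two compatible without changing the sentence.

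**Conclusion.** The point holds as an internal contradiction. Team-wide blinding until 24 weeks cannot coexist with the allocation videoconference, the invitation to the first 10 intervention dyads, the session support, the T1 interviews and the arm-specific advice after a death. If the videoconference covers all dyads, every allocation is known to at least one person working on the study before the primary time point. If it covers only self-referred dyads, the contradiction remains, but for fewer dyads.

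The conclusion assumes that the research officer, trial manager and interviewers belong to the research team, since the article describes no other group. It does not show that nobody is blind, and it does not show that the primary comparison is biased. The design remains usable. The sentence should be corrected because it states a property that the design does not have.

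**What to change.** Replace the blinding sentence with one that says:

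- participants are not blind, and neither are the operational staff who disclose allocation, support sessions or hold interviews;
- which roles do stay blind, and until when. The analysing statistician, working with masked arm codes, is one possibility, but only if the sponsor confirms that this is so. Otherwise one unsupported claim would replace another.

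Reconcile this statement with Setting and Recruitment Procedures, Stage 3 and Ethical Considerations, and make clear whether the second videoconference applies to both recruitment routes.

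Add two short rules: T1 questionnaires are completed before any T1 interview, and any T1 or T2 questionnaire reminders follow the same schedule in both arms.

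The cost is a change of wording and some attention to scheduling. The sample size and outcomes do not change. The downside is that the stated blinding becomes less favourable than the present text suggests.
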